# T-ScEmo4ALL Plus+: Treatment for social cognition disorders in patients with acquired brain injury and neuropsychiatric problems – A single case experimental design (SCED) study protocol

**DOI:** 10.1371/journal.pone.0358008

**Published:** 2026-09-18

## Abstract

**Introduction:**

Many patients with acquired brain injury (ABI) suffer from impaired social cognition, which may result in reduced social participation, quality of life and quality and stability of partner relationships. Social cognition problems often co-occur with, and in some cases contribute to, neuropsychiatric symptoms such as emotional dysregulation, disinhibition, and irritability, which may further complicate social functioning. Effective interventions targeting social cognition are therefore of particular importance for ABI patients with comorbid neuropsychiatric symptoms. The Treatment Social cognition and Emotion regulation (T-ScEmo) has shown promising effects on social cognition and emotion regulation in patients with traumatic brain injury (TBI), but has not yet been studied in ABI patients with comorbid neuropsychiatric problems. Therefore, the main aim of the current study is to examine the effect of T-ScEmo on social functioning in patients with ABI and comorbid neuropsychiatric problems.

**Methods and analysis:**

A non-concurrent, randomized, multiple-baseline single-case experimental design (SCED) will be employed to investigate the effectiveness of T-ScEmo in this study. At least 8 participants and a significant other will be randomly assigned to one of three baseline lengths. The primary outcome measures (social functioning, neuropsychiatric problems, relationship quality) will be assessed daily during baseline and twice a week during the treatment and maintenance phases. Secondary outcomes will be assessed at T0 (pre-treatment), T1 (post-treatment), and T2 (1-year follow-up). Both patients and the significant other will complete all outcome measures.

**Discussion:**

T-ScEmo may offer a valuable addition to neurorehabilitation practices for this specific target group of patients. Forthcoming results may contribute to more personalized and effective treatment strategies for the growing number of patients with ABI and comorbid neuropsychiatric problems.

**Trial registration:**

The study is registered in the database of clinicaltrials.gov (Treatment for Social Cognition Disorders (T-ScEmo) in Patients With Acquired Brain Injury and Comorbid Neuropsychiatric Problems | ClinicalTrials.gov) under identifier NCT06923683. Date registered: 04/17/2025.

## Introduction

Social cognition is a fundamental aspect of human behavior, encompassing the ability to attend to, process and interpret social information to understand other people, and react to their expectations or needs [1]. Social cognition is a complex, multifaceted construct that is challenging to define concisely. It can generally be described as “the ability to function appropriately in social and interpersonal situations” [2]. More specifically, social cognition consists of three interrelated aspects in which individuals with acquired brain injury (ABI) frequently experience difficulties [3,4]. First, perception of socially relevant information (e.g., reading facial expressions, body language, and emotional cues). Second, understanding and interpreting others’ thoughts and feelings (e.g., empathy, theory of mind (ToM), mentalization). Third, responding to social information (e.g., appropriately adjusting behavior to the situation) [1,5]. To address the complexity of social cognition, the Hierarchical Interdependent Taxonomy of Social cognition (HITS) model was developed. This biopsychosocial framework integrates expert consensus with empirical evidence and highlights the interdependence of key social cognitive processes. It offers a structured, theory-driven basis for assessment and intervention in both research and clinical settings [6].

Problems in social cognition are prevalent across a wide range of neurological, neuropsychiatric and developmental brain disorders, including traumatic brain injury (TBI), stroke, brain tumors, and autism spectrum disorders [7–9]. In ABI, especially when the orbitofrontal and ventromedial prefrontal cortices are affected, social cognition impairments are common [10,11]. Prevalence estimates suggest that 13%−47% of patients with ABI show difficulties in domains such as theory of mind, empathy, and facial emotion recognition [12,13]. However, these percentages likely underestimate the true prevalence, as social cognition is often not considered in routine neuropsychological assessments [14].

Social cognition problems represent a major source of burden for individuals with ABI and their families. Increasing evidence suggests that such problems contribute to socially inappropriate or disruptive behavior (e.g., disinhibition, lack of empathy, apathy) [15,16], which is often viewed as problematic by relatives [17]. These problems negatively impact the quality and stability of partner relationships, social participation, return to work, and quality of life [17–22]. Thus, given the central role of social cognition in everyday functioning, the treatment of deficits in social cognition following ABI is of critical importance [14].

Although the number of treatment studies targeting social cognition is growing, existing studies still face important limitations. Most studies focused on a single aspect of social cognition, included small sample sizes, lacked (long-term) follow-up data, and/or showed limited generalization to everyday-life social behavior [23–29]. In response, Westerhof-Evers et al. [5] developed a comprehensive, multifaceted intervention called T-ScEmo, targeting impairments in social cognition and emotion regulation. A randomized controlled trial (RCT; N = 61) demonstrated its effectiveness in improving facial affect recognition, ToM, empathic behavior, and societal participation of patients with TBI. Unlike most interventions, T-ScEmo addresses three core aspects of social cognition, includes involvement of significant others, and strongly emphasizes generalization to daily life. As a result, T-ScEmo is now established as an evidence-based treatment for social cognition impairments in individuals with TBI in the Netherlands.

Social cognition problems often co-occur with, and in some cases contribute to, neuropsychiatric problems after ABI. Patients with comorbid neuropsychiatric problems are however often excluded from treatment studies on social cognition. In this study, neuropsychiatric problems are broadly defined to include a wide spectrum of behavioral problems — such as disinhibition and aggression — as well as formal DSM-5 diagnoses including anxiety disorders, depression, and personality disorders. Neuropsychiatric behavioral problems, such as disinhibition, alexithymia, and aggression, frequently overlap with and/or result from underlying social cognition impairments [30,31]. Yet, neuropsychiatric symptoms are not exclusively attributable to social cognition deficits; many patients exhibit neuropsychiatric disturbances that arise independently of social cognitive impairments, reflecting a multifactorial pathophysiology [32]. In this study, patients present with neuropsychiatric problems of such severity and complexity that treatment within a specialized neuropsychiatric setting is indicated. These patients differ from those commonly seen in standard rehabilitation settings, who may also present with social cognition deficits, but exhibit less severe and disruptive neuropsychiatric symptoms.

A recent literature review by Torregrossa and colleagues [33] reported that 25% to 88% of individuals with moderate to severe ABI experience neuropsychiatric problems, including aggression, disinhibition, irritability, alexithymia, depression, anxiety, PTSD, or suicidality [33]. Moreover, a retrospective study found that 72.5% to 81.8% of patients with ABI and neuropsychiatric problems score low or very low on emotion recognition, with significantly lower scores in other domains of social cognition (e.g., empathy, ToM) compared to patients with ABI without such comorbidities [34]. Despite the high prevalence and severity of these problems, patients with ABI and comorbid neuropsychiatric problems are often excluded from treatment studies on social cognition. Only a few studies have evaluated interventions in this subgroup: two studies found positive effects of group-based treatments on social communication skills in patients with ABI and comorbidities, but only focused on social communication skills [35], and one RCT demonstrated the effectiveness of a treatment in this population, but included a small sample (N = 43) and lacked follow-up data [27]. This limited evidence is striking, especially given that social cognitive problems may be more pronounced and persistent in patients with ABI and comorbid neuropsychiatric problems [34].

The exclusion of patients with ABI and neuropsychiatric comorbidities in ABI research [5,21,25,28] is often justified on ethical or methodological grounds – such as concerns about decisional capacity or confounding effects on outcome measures. However, these exclusions limit the external validity and clinical applicability of research findings. For example, a systematic scoping review of 428 inpatient stroke rehabilitation RCTs found that 83% excluded patients with comorbidities, 54% excluded those with cognitive impairment, and 36% excluded those with prior stroke [36]. These exclusions risk creating a research-practice gap, whereby interventions validated in highly selective and homogeneous populations may not be applicable to real-world clinical settings.

Although the effectiveness of T-ScEmo has been demonstrated in individuals with TBI, it remains unknown whether the treatment is also effective in individuals with ABI and comorbid neuropsychiatric problems. Therefore, the primary aim is to examine the effect of T-ScEmo on social functioning in patients with ABI and comorbid neuropsychiatric problems (RQ1). Secondary aims include examining the effects of T-ScEmo on neuropsychiatric problems and quality of partner relationships in this population (RQ2).

### Hypotheses

#### Primary research question (RQ1).

Based on previous research in patients with TBI [5,21], we hypothesize that T-ScEmo will reduce social cognition problems in patients with ABI and comorbid neuropsychiatric problems. While T-ScEmo is a compensatory strategy training and thus not expected to directly improve underlying cognitive mechanisms, improvements in social behavior are anticipated due to skill acquisition, practice in daily life, and involvement of significant others. However, as the first modules specifically targets facial emotion recognition, we also expect improvements on the FEEST (i.e., emotion recognition).

We also expect improvements in social communication and interaction, as the treatment targets emotion recognition, ToM, perspective taking, awareness, inhibition of undesired social behavior and socially desired behavior. Improved compensation for deficits is expected to enhance participation in social contexts.

#### Secondary research questions (RQ2).

In addition, we hypothesize that T-ScEmo will reduce neuropsychiatric problems in patients with ABI and comorbid neuropsychiatric problems. Social cognition problems often co-occur with, and in some cases contribute to, with neuropsychiatric symptoms following acquired brain injury (ABI). These social cognition difficulties are also commonly observed in other psychiatric disorders such as autism spectrum disorders and schizophrenia [8,37]. Although our study focuses on patients with ABI, improvements in social cognition have the potential to alleviate distress and behavioral dysregulation associated with neuropsychiatric symptoms across different conditions [28].

Finally, we hypothesize that the quality of partner relationships will improve. Involving a partner in the treatment may increase mutual understanding and support, while better social responsiveness on the part of the patient can positively influence relationship quality.

## Methods

### Study design

#### Phases and measurements.

A non-concurrent, randomized, multiple-baseline single-case experimental design (SCED) will be used in this study. In a SCED study, participants are repeatedly measured during all phases. The current study will be divided into four phases: baseline, treatment, maintenance, and follow-up. Repeated and frequent measures of the target behavior will be conducted within each phase. The rule of thumb is to collect data at least three, preferably five times per phase [38,39]. The primary outcome measure will be assessed daily during the baseline phase and twice a week in the treatment and maintenance phase. All secondary outcome measures will be assessed at T0 (baseline); a subset will also be assessed at T1 (post-treatment) and T2 (follow-up; 3–5 months post-treatment). See Table 1 and Fig 1 for an overview of the phases and measurements included in this study, including both primary and secondary outcome measurements.

**Table 1 pone.0358008.t001:** Overview of the phases and measures T-ScEmo4ALL Plus^+^.

Tests and questionnaires	Description	T0	Baseline (A)	Treatment (B)	T1	Maintenance (C)	Follow-up (D)/T2
Phase duration (weeks)			2 up to 4	20 up to 25		13 up to 21	

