### Procedure

Healthcare professionals at the Center of Excellence for Brain Injury and Neuropsychiatry who identify patients with an indication for treatment of social cognition problems will inform the researcher. Recruitment started on 1 January 2025. Participant recruitment is ongoing and will continue until the end of December 2026. Completion of data collection is anticipated in April 2027, and the study results are expected to be available by December 2027.

Psychologists will screen patients for eligibility based on the in- and exclusion criteria. Eligible patients will receive detailed information about the study. Then, patients will be invited to participate voluntarily during outpatient or clinical appointments. Those who consent to participate will be asked to sign an informed consent form. Upon providing informed consent, participants will be randomized to a baseline phase of varying duration, after which the T-ScEmo intervention starts, followed by maintenance and follow up phases.

Baseline measurements include a neuropsychological assessment, unless one has been conducted within six months prior to the start of the study. Furthermore, during this initial session, the therapist, together with the patient and the significant other, will formulate three treatment goals (TGA; Treatment Goal Attainment). Before, during, and after treatment participants complete multiple neuropsychological tests during a face-to-face appointment with a (trained) psychological assistant, intern or neuropsychologist. Participants and the significant other will complete a series of questionnaires digitally (see Table 1). They are free to choose when to complete the questionnaires and may pause and resume as needed.

In phases B and C, self-report scales are administered twice a week and must be completed before the next treatment session to ensure timely data collection. Post-treatment measurements will be conducted to evaluate the maintenance of treatment effects and to maintain consistency in the number of measurements across participants. A follow-up measurement will be conducted 3–5 months after treatment completion to evaluate long-term efficacy. Patients who choose not to participate will still receive T-ScEmo treatment, as it is considered standard care.

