### Primary outcome measure

*Satisfaction with social functioning* is assessed using a Social Functioning Scale (SFS), in which patients and significant others rate the patient’s functioning in social situations on a 10-point Likert scale ranging from 1 (“not at all”) to 10 (“entirely”). The item presented is: “How satisfied are you today with your (or your significant other’s) functioning in social situations?” To ensure a sufficient number of data points, as recommended for SCED studies, the SFS will be completed frequently: daily during phase A (2–4 weeks) and twice per week during phases B (20–25 weeks) and C (13–21 weeks). The SFS will be completed by both the patient and a significant other online (M-Path).

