Given the small and heterogeneous sample in this highly specialized clinical setting, an RCT was considered unfeasible. Instead, a single-case experimental design (SCED) was chosen, incorporating randomized baseline lengths to enhance internal validity. One challenge of the SCED approach is the intensive data collection schedule, including daily and biweekly measurements. This may reduce response rates due to motivational issues or limited illness insight. To mitigate this risk, adherence will be closely monitored by both the therapist and researcher on a weekly basis. For inpatients, nursing staff may support data collection, while the M-path app provides automatic notifications to encourage timely questionnaire completion. Multiple assessment points have been incorporated to ensure that sufficient data is collected even in the event of missing responses.

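### Follow-up is counted as a repeatedly measured phase, but the plan appears to schedule only one primary-outcome rating per rater in it

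*Protocol article*

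**What the plan says.** All references are to the protocol article.

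- **Study design, Phases and measurements:** "The current study will be divided into four phases: baseline, treatment, maintenance, and follow-up". The same paragraph adds "Repeated and frequent measures of the target behavior will be conducted within each phase" and "The rule of thumb is to collect data at least three, preferably five times per phase".
- **The same section, on frequency:** "The primary outcome measure will be assessed daily during the baseline phase and twice a week in the treatment and maintenance phase". No frequency is given for follow-up. The Primary outcome measure section repeats the pattern: it gives a frequency and a duration for A, B and C and does not list D.
- **Table 1:** phase D and visit T2 share one column, with no phase duration. The SFS cell there is a bare symbol for both raters, while the A, B and C cells carry a frequency. The Neuropsychiatric Problems Scale (NPS) and the Relationship Quality Scale (RQS) follow the same pattern. One-off tests such as the FEEST carry the same kind of bare symbol.
- **Procedure:** "A follow-up measurement will be conducted 3–5 months after treatment completion to evaluate long-term efficacy", in the singular.
- **Discussion, on missing data:** "Multiple assessment points have been incorporated to ensure that sufficient data is collected even in the event of missing responses".

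**The concern.** The design paragraph promises something for every phase that the schedule appears to deliver for only three of the four. The phase left out is the one named as the basis for long-term efficacy, and the Discussion expects gains to last.

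The SFS is one item, scored 1 to 10, about satisfaction on that day. The Visual analyses section works with level, trend, variability and overlap. A phase with one point has no trend and no variability, and its level and overlap rest on one day's answer. The Discussion expects lower response from poor motivation or limited insight and relies on having several assessment points to absorb it. Within D there is nothing to absorb a miss. At stake is how far the study can speak, on its primary outcome, about the follow-up period.

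**Working it through.** **1. Planned SFS ratings per rater (frequency × stated duration)**

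| Phase | Input | Ratings | Against 3 / 5 |
|---|---|---|---|
| A | daily, 2–4 weeks | 7 × 2 = 14 to 7 × 4 = 28 | above both |
| B | 2 per week, 20–25 weeks | 40 to 50 | above both |
| C | 2 per week, 13–21 weeks | 26 to 42 | above both |
| D/T2 | bare symbol, one measurement | 1 (inferred) | 2 short / 4 short |

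Using the randomized day bands in the Randomization section, A would be 16 to 33. The conclusion is the same.

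**2. How close phase C comes to T2.** Assume C starts when treatment ends. At 4.345 weeks per month, C ends 13/4.345 = 3.0 to 21/4.345 = 4.8 months after treatment. The Study design and Procedure sections put T2 at 3–5 months, so late C ratings lie near T2. The Abstract puts T2 at one year. On that reading nothing covers the gap.

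**3. Precision of the phase D value.** The article gives no day-to-day SD, so SD = 1.5 points is an assumption.

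- One rating: 1.96 × 1.5 = ±2.94.
- Mean of five, days independent: 1.96 × 1.5/√5 = ±1.31.
- Mean of five consecutive days, lag-1 correlation 0.5 (assumed, decaying geometrically): the variance inflation is 1 + 2(0.8×0.5 + 0.6×0.25 + 0.4×0.125 + 0.2×0.0625) = 2.225. The range is 1.96 × 1.5 × √(2.225/5) = ±1.96, about ±2.0.

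For any other SD the half-widths are 1.96 SD for one rating and 0.88 SD to 1.31 SD for five. Five days therefore narrow the range to between 45% (1/√5) and 67% (√(2.225/5)) of its single-rating width.

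**4. Missing ratings.** The article gives no non-response rate. Assume a rate m of 10–40% per rating, with independent misses. With k scheduled ratings, a rater has no D value with probability m^k. Both members of a dyad lack one, with k = 1, with probability m².

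| m | One rater, k = 1 | Both raters, k = 1 | One rater, k = 5 | At least 3 of 3 / of 5 obtained |
|---|---|---|---|---|
| 10% | 10% | 1% | 0.001% | 73% / 99% |
| 20% | 20% | 4% | 0.03% | 51% / 94% |
| 30% | 30% | 9% | 0.24% | 34% / 84% |
| 40% | 40% | 16% | 1.0% | 22% / 68% |

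At 20–30% and the minimum of 8 patients, 8 × 0.2 = 1.6 to 8 × 0.3 = 2.4 patients would lack their own D rating. Both ratings would be lost in 8 × 0.04 = 0.3 to 8 × 0.09 = 0.7 dyads. Independence flatters both comparisons: someone who drops out before T2 misses all five ratings, and members of a dyad may miss together.

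**5. Effect on the planned test.** The Statistical analyses section sets baseline against treatment and follow-up together. One D point beside 40–50 treatment ratings carries almost no weight there.

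**The case against.** A reader might infer four stronger things. The document does not support them.

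- **That one missed prompt leaves no primary follow-up data.** The significant other also rates the SFS. A miss empties one rater's D value, and the other rater's remains.
- **That the plan breaks a binding minimum.** Three points is a rule of thumb taken from cited sources. The firm statement is the promise of repeated and frequent measurement in each phase, and the mismatch is with that.
- **That the main inference is damaged.** It rests on the randomized change from baseline to treatment, and the pooled test barely uses D.
- **That long-term efficacy hangs on one rating.** T2 repeats the BAFQ-SOC, DEX, IRI, LCQ, Cartoon test, FEEST, DMSCQ and NPI-Q, to which the Reliable Change Index is applied, and late maintenance data lie close by.

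It is also fair to say that T2 is a planned assessment with face-to-face testing, and that participants choose when to fill in questionnaires. App notifications and weekly adherence monitoring are described too. An ordinary non-response rate may therefore be too pessimistic for T2. Finally, the single rating is inferred: T0 carries a bare symbol too, and Fig 1 and the full protocol are not shown. The singular wording in the Procedure section and the missing frequency and duration for D make one occasion the natural reading.

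All of this limits the consequence. It does not reconcile the design paragraph with the schedule.

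**Conclusion.** The point holds in a limited form. Follow-up is called a repeatedly measured phase, yet the schedule indicates one SFS, one NPS and one RQS rating per rater. On these scales D can show no trend or variability of its own, and the safeguard against missing responses does not reach it.

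Under the assumed SD of 1.5, a single rating carries about ±2.9 points on a 10-point scale, against ±1.3 to ±2.0 for five consecutive days. The gain is real but smaller than independent days would suggest. The practical loss is modest if T2 falls at 3–5 months, and larger if the Abstract's one year is right. The SD, the correlation and the non-response rates are assumptions; the counts of ratings in phases A to C are the plan's own. This is a cheap improvement and does not threaten the primary comparison.

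**What to change.** Schedule about five M-Path ratings of the SFS, NPS and RQS, by both raters, on days around T2. Five is better than three because it leaves room for misses (step 4 of the working). The cost is four extra days of three single-item ratings in an app already in use, with slight added burden for participants.

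If that is not wanted, change the wording. Limit the promise of repeated measurement to phases A to C, describe T2 as a follow-up visit, and base long-term SFS statements on the last weeks of phase C. This costs only an edit.

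In either case, reconcile the timing of T2 between the Abstract and the Methods, because the second option works only if late maintenance data lie near T2.
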